## Abstract

**Background:**

People with lung cancer have substantial symptom burden and more unmet needs than the general cancer population. Physical activity (PA) has been shown to positively influence quality of life (QOL), fatigue and daily functioning in the curative treatment of people with breast and colorectal cancers and lung diseases, as well as in palliative settings. A randomised controlled trial (RCT) is needed to determine if lung cancer patients benefit from structured PA intervention. The Physical Activity in Lung Cancer (PAL) trial is designed to evaluate the impact of a 2-month PA intervention on fatigue and QOL in patients with non-resectable lung cancer. Biological mechanisms will also be studied.

**Methods/design:**

A multi-centre RCT with patients randomised to usual care or a 2-month PA programme, involving supervised PA sessions including a behavioural change component and home-based PA. QOL questionnaires, disease and functional status and body composition will be assessed at baseline, 2, 4 and 6 months follow-up. The primary endpoint is comparative levels of fatigue between the 2 arms. Secondary endpoints include: QOL, functional abilities and physical function. Exploratory endpoints include: anxiety, depression, distress, dyspnoea, PA behaviour, fitness, hospitalisations, survival, cytokines and insulin-like growth factor levels.

**Discussion:**

This study will provide high-level evidence of the effect of PA programmes on cancer-related fatigue and QOL in patients with advanced lung cancer. If positive, the study has the potential to change care for people with cancer using a simple, inexpensive intervention to improve their QOL and help them maintain independent function for as long as possible.

**Trial registration:**

Australian New Zealand Clinical Trials Registry No. ACTRN12609000971235

## Background

Lung cancer is the leading cause of cancer-related death worldwide. In the United States alone it was estimated there would be 226,160 new lung cancer cases and 160,340 lung cancer deaths in 2012 [1]. The majority (60%) of lung cancer patients present with advanced, incurable disease resulting in a median survival of only 9–12 months [2]. In this context, the aim of anti-cancer treatment is to improve or maintain quality of life (QOL) in addition to prolonging survival.

Fatigue is one of the most common and distressing patient-reported symptoms associated with cancer and its treatment [3-5]. People with lung cancer report a higher prevalence and longer duration of cancer-related fatigue, leading to more functional impairment when compared to other cancer patients [6]. There is growing evidence that physical activity can improve fatigue in people with cancer, [7-9] and in those with chronic obstructive pulmonary disease (COPD) [10]. However, no study has evaluated the benefits of a lifestyle physical activity programme for people with non-resectable lung cancer. This study will determine if physical activity improves fatigue, in people with non-resectable lung cancer.

In the past five years several large observational studies have reported that physical activity reduces the risk of cancer recurrence, death from cancer, and death from all causes for breast and colon cancer patients [11-16]. These studies have shown consistently that more than 9 metabolic equivalent task (MET) hours/week of physical activity (e.g. walking at a moderate pace for 2.5 hours/week) is associated with improved health outcomes. This is similar to the health guidelines of 150 minutes of moderate intensity physical activity per week or 60 minutes of vigorous physical activity per week [17].

A burgeoning literature has examined the effects of physical activity on supportive care outcomes in people with cancer including physical fitness, physical function, fatigue and QOL [8,18-21]. Observed benefits of physical activity include improved cardiovascular and pulmonary function, musculoskeletal strength, maintenance of mobility and independence, and improved psychological well-being and QOL [9,22,23]. Systematic reviews and meta-analyses have concluded that physical activity interventions during and after cancer therapies often result in meaningful and reliable improvements in several supportive care outcomes [8,9,19,20,22-25]. These benefits include observed changes in physiologic measures, objective performance indicators, self-reported functioning and symptoms, psychological well-being and overall QOL. However, these studies did not include people with advanced lung cancer.

A large body of evidence documents the benefits of physical activity as a component of pulmonary and cardiac rehabilitation in similar clinical populations, which demonstrate improved QOL, functional status, and symptom control including dyspnoea in patients with COPD. A Cochrane review of 31 randomised controlled trials in chronic obstructive pulmonary disease patients found those receiving pulmonary rehabilitation had statistically and clinically significant improvements in QOL, including dyspnoea, fatigue and patient control over disease [10].

Despite the benefits of physical activity, only 20-32% of all cancer survivors report meeting physical activity guidelines [18,26-28]. A recent study in lung cancer survivors found that 73% did not meet the United States physical activity guidelines, and 51% did not participate in any moderate or vigorous physical activity at all [29]. Lung cancer survivors who met the physical activity guidelines reported significantly better QOL across multiple domains compared to those who did not meet the guidelines [30]. This suggests that there are considerable opportunities for improving the physical activity behaviour of lung cancer patients and possibly improving their QOL.

Most physical activity studies have been performed in cancer populations with potentially curative disease, particularly breast and colorectal cancer survivors. By comparison, people with advanced incurable lung cancer are older (median age of 70 years) and more likely to have co-morbidities such as chronic obstructive pulmonary disease and cardiovascular disease. However, physical activity has been found to be beneficial in older cancer patients, [3] and in a palliative population [21]. Cardiopulmonary exercise testing in people with advanced cancer, including lung cancer, has been shown to be safe and feasible, which suggests that most people would be able to follow a programme emphasising moderate intensity physical activity [31].

The biological mechanisms by which physical activity may modify cancer risk or disease progression, or improve symptom control, include changes in insulin-like growth factor (IGF) levels, immune regulation, sex and metabolic hormone levels, prostaglandin ratio and obesity [16,32-35]. More specific to lung cancer, physical activity improves pulmonary function and perfusion, [36] and it is hypothesised that physical activity may up-regulate antioxidants and free scavengers to help counteract the effects of cigarette smoke [37]. Physical activity may also decrease the risk of pneumonia and venothrombotic events, thereby improving overall survival and QOL in patients with non-resectable lung cancer.

Our aim is to evaluate a physical activity programme in people with non-resectable lung cancer to determine if it improves fatigue and quality of life. Our hypotheses are that people who undergo the physical activity intervention compared to those who do not, will: 1) report less fatigue; 2) have better health-related quality of life; 3) have improved overall survival; and, 4) have less decline in their level of physical function over time.

## Methods/design

This multi-site, randomised controlled trial is being led by the Survivorship Research Group (SuRG) at the University of Sydney, Australia. Funding was obtained from a Young Investigator Award from the Lance Armstrong Foundation. The study was prospectively registered with the Australian New Zealand Clinical Trials Registry, registration number ACTRN12609000971235. Ethics approval has been obtained from Concord Repatriation General Hospital Human Research Ethics Committee for each participating institution under the New South Wales Health multi-site ethics approval scheme (HREC reference number: 08/CRGH/242).

Participants are recruited from lung cancer clinics at 4 Sydney hospitals, commencing May 2009 until achievement of planned sample size.

Consenting, medically fit people with non-resectable lung cancer, including non-small cell lung cancer (NSCLC) and small cell lung cancer (SCLC) are randomised to usual care or a 2-month physical activity intervention (Figure 1). People with Stage III NSCLC or locally advanced SCLC being treated with curative intent must have completed combination chemo-radiotherapy a minimum of 4 weeks prior to randomisation, and have an incomplete response on staging CT scans. People with metastatic disease being treated palliatively may be receiving chemotherapy, radiotherapy and/or biological agents. All subjects must be medically fit to participate in a physical activity program, as assessed by the Physical Activity Readiness Questionnaire (PAR-Q) [38] and their treating physician. Major exclusion criteria are: Eastern Co-operative Oncology Group (ECOG) performance status ≥3, life expectancy < 6 months or insufficient English fluency to complete the questionnaires. Complete inclusion and exclusion criteria are outlined in Table 1. Randomisation is stratified for disease stage (locally advanced: NSCLC Stage III/ limited SCLC without a complete response to treatment versus metastatic disease: NSCLC Stage IV and extensive SCLC), ECOG performance status (0–1 versus 2), and cancer centre. It is performed by an external academic organisation using an interactive voice response system.

**Figure 1 F1:**
[figure not shown]
**Study flowchart.** PRO = patient reported outcomes.

**Table 1 T1:** Study inclusion and exclusion criteria

**Inclusion criteria**	**Exclusion criteria**
Diagnosis of invasive lung cancer (NSCLC or SCLC) that, in the opinion of the oncology team, is non-resectable and non-curable.	European Co-operative Oncology Group (ECOG) Performance Status of > 3.
People with Stage III NSCLC or limited SCLC who have evidence of residual disease and have completed treatment with chemotherapy and or radiotherapy a minimum of 4 weeks prior to commencing the study.	Pre-existing significant co-morbid conditions precluding participation in a physical activity programme, as determined by the investigator.
People with advanced disease being treated palliatively may be receiving chemotherapy, biological agents and/or best supportive care.	Insufficient English fluency to complete the questionnaires.
Aged at least 18 years.	Life expectancy of < 6 months.
Medically fit to participate in a physical activity programme, as determined by their oncologist.	Inability to complete the baseline exercise test (6 Minute Walk) done prior to randomisation.
Ability (i.e. sufficiently fluent) and willingness to complete the patient- reported outcome questionnaires, physical activity questionnaires and logs in English.	
Give written informed consent.	
Completion of the 3 Questionnaire assessment within 14 days of registration.	
Completion of the Physical Activity Readiness Questionnaire within 14 days of registration.	

*NSCLC*, Non-small cell lung cancer.

*SCLC*, Small cell lung cancer.

### Control – standard of care

All participants will have routine follow-up as per local cancer centre practice and receive cancer-specific education materials regarding nutrition (Eat For Health) and exercise (Move Your Body) published by Cancer Council Australia (http://www.cancer.org.au/home.htm) to encourage adoption of a healthy lifestyle.

### Intervention

#### Theoretical framework

The physical activity programme is based on the Theory of Planned Behaviour, [39] and modelled after the successful behaviour change programme developed by the Diabetes Prevention Programme [40].

Participants randomised to the physical activity intervention arm will participate in a 2-month individualised physical activity and behavioural support programme with a Physical Activity Consultant (PAC).

The goal of the intervention will be to increase the participant’s physical activity over the 2-month intervention by a minimum of 3 MET hours per week compared to baseline. While this may be less than the recommended physical activity guidelines for some participants, those capable of increasing their MET hours further will be encouraged to do so.

The physical activity program will consist of supervised physical activity (30 to 45 minutes duration) and behaviour support sessions (15 to 30 minutes) once a week for 8 weeks, as well as unsupervised home physical activity sessions. The physical activity program (including supervised and unsupervised sessions) will be tailored to the participant’s baseline fitness, performance status and physical activity preferences, and take account of personal facilitators and barriers to physical activity. The study emphasises aerobic physical activity. Consequently it is expected that most participants will engage in walking as their preferred form of physical activity; however, other forms of aerobic activity such as swimming, cycling or running are acceptable. The program also incorporates advice about resistance exercises to encourage participants to maintain muscle function and strength.

The weekly structured sessions include physical activity as well as behaviour support sessions that use behaviour lifestyle change principles. It is the behaviour support sessions that will be the primary focus of the program promoting unsupervised physical activity. A full list of behaviour change session titles and their learning goals is outlined in Table 2. Participants will be supplied with a physical activity and behaviour change guidebook titled “Exercising with Lung Cancer”, a pedometer and physical activity diary for use throughout the intervention.

**Table 2 T2:** Behaviour support sessions

**Session***	**Session title**	**Session learning goals**
		**By the end of the session participants should have**:
1	Introduction to the program	· Learned about the gymnasium / fitness facility;
		· Learned how to monitor intensity using the Borg Scale;
		· Learned how to properly stretch;
		· Learned about the PAL Study objectives;
		· Learned how to complete the daily PA Diary.
2	Exercising properly	· Learned what to wear when doing PA;
		· Learned the basics of proper hydration;
		· Learned about safety when doing PA.
3	Goal setting and planning	· Understood the importance of setting goals;
		· Learned how to create short and long term goals based on the SMART principle;
		· Learned how to create action steps to achieve a PA goal.
4	Pedometers and walking	· Learned about the health benefits of walking;
		· Learned how to use a pedometer;
		· Create a plan to increase the amount of steps per day.
5	Benefits of physical activity and overcoming barriers to physical activity	· Understood the benefits of PA to the general population;
		· Learned more about the benefits of PA specific to people with lung cancer;
		· Identified what their personal barriers to PA are;
		· Worked through and brainstormed ideas how to overcome these barriers.
6	Environmental scan	· Learned what PA opportunities exist in their local environment;
		· Learned how to make use of indoor fitness facilities or sports stores.
7	Social support and having fun with physical activity	· Learned the importance of social support for maintaining a PA program;
		· Identified what social support they may be able to utilise;
		· Identified what makes PA fun for them;
		· Brainstormed how to increase their enjoyment of PA.
8	Stimulus control and decision balance sheet	· Learned what stimulus control is and how it affects behaviour;
		· Learned how to establish appropriate stimuli;
		· Understood the benefits of using a decision balance sheet;
		· Learned how to create and use a decision balance sheet for themselves.

* Order of behaviour change session delivery can be tailored to suit the most pressing educational and behavioural needs of participants.

### Assessments

Outcomes will be assessed at baseline (prior to randomisation), 2, 4 and 6 months (Figure 1). Baseline assessments involve a medical history and examination. At all assessments, disease and treatment status will be recorded and subjects will complete patient reported outcome (PRO) questionnaires, a standardised fitness test (6 Minute Walk Test, [41] Senior’s Fitness Test, [41] hand grip strength [42]), and donate blood for biomarker analysis. All subjects will wear an Actigraph GT1M accelerometer [43] (Actigraph LLC, Pensacola, FL, USA) on the right hip to objectively determine physical activity for 7 full days prior to each assessment. Survival status will be obtained from the medical records, with follow up until the time of the final analysis.

#### Primary and secondary endpoints

The primary endpoint will be the level of self-reported fatigue as assessed by the Functional Assessment of Cancer Therapy - fatigue (FACT-F) subscale [44,45]. The primary outcome will be a comparison of fatigue in the intervention and control arms at the conclusion of the intervention (i.e. at the 2-month assessment).

Secondary endpoints will include the following Patient Reported Outcomes:

• QOL (European Organisation for Research and Treatment of Cancer –Quality of life questionnaire – Core (EORTC-QLQ-C30) and Lung module (LC-13 subscale) [46],

• activities of daily living and instrumental activities of daily living[47].

• physical function (6 Minute Walk Test) [41].

Other exploratory endpoints relating to physical activity and fitness will include:

• anxiety and depression (General Health Questionnaire 12) [48];

• distress (Distress Thermometer) [49],

• perceived cognitive function (FACT-Cognition v3) [50],

• sleep quality (Pittsburgh Sleep Quality Index) [51],

• dyspnoea (University of California San Diego Shortness of Breath Questionnaire [52] and physical activity and sedentary behaviour (Actigraph GT1M accelerometer; Active Australia questionnaire [53], sedentary behaviour questionnaire [54]);

• physical activity attitudes (Social Cognitive Determinants of Exercise questionnaire) [30,55]

• physical fitness (6 Minute Walk Test, Seniors Fitness Test, [41] hand grip strength);

• pulmonary function (Forced Expiratory Volume in 1 second, Forced Vital Capacity);

• general health, functional and performance status (anthropmetric measurements, Colinet co-morbidity score [56], ECOG performance status, admissions to hospital/hospice and survival data); and

• mechanisms and prognostic biomarkers (Glasgow Prognostic Score [C-reactive protein, albumin], selected cytokine levels, insulin-like growth factors).

Table 3 gives an overview of all outcome assessments.

**Table 3 T3:** Assessments

	**Investigations**	**Timing**
History and Physical Exam including:	· Height (baseline only)	0,2,4, 6 months
	· Weight and Body Mass Index (BMI)	
	· Blood Pressure and Heart Rate	
	· Oxygen saturation (SaO2) (on room air)	
	· Concomitant medications (any changes to baseline meds)	
	· Colinet Co-morbidity Score	
	· Eastern Cooperative Oncology Group Performance Status (ECOG PS)	
	· Disease status	
	· Current treatments	
Fitness Testing	· 6-minute walk test (6MWT)	0,2,4, 6,months
	· Senior’s Fitness Test	
	· Hand grip strength	
Pulmonary Function	· Forced Expiratory Volume at 1 second (FEV_1_)	0,2,4,6 months
	· Forced Vital Capacity (FVC)	
Adverse Events	· Adverse events will be recorded and graded using National Cancer Institute Common Terminology Criteria for Adverse Events Version 3.0 (NCI CTCAE v3.0)	0,2,4, 6 months
Patient Reported Outcomes	· Functional Assessment of Cancer Therapy - Fatigue (FACT-F subscale)	0,2,4,6 months
	· Quality of Life (QOL) European Organisation for Research and Treatment of Cancer –Quality of life questionnaire – Core (EORTC-QLQ-C30) and Lung module (LC-13 subscale)	
	· Depression and Anxiety (General Health Questionnaire - GHQ12)	
	· Sleep Quality (Pittsburgh Sleep Quality Index - PSQI)	
	· Cognitive Function (Functional Assessment of Cancer Therapy – Cognitive scale - FACT-COG v3)	
	· Distress (Distress Thermometer)	
	· Dyspnoea (The University of California, San Diego Shortness of Breath Questionnaire -SOBQ)	
	· Activities of Daily Living (ADLs) and Independent Activities of Daily Living (IADLs)	
	· Sedentary time (Sitting Questionnaire)	
	· Physical activity attitudes (Social Cognitive Determinants of Exercise questionnaire)	
Physical Activity Behaviour/ Adherence	· Physical activity participation (Active Australia)	0,2,4, 6 months
	· Accelerometer -for one week prior to each assessment	
Other Investigations	· Fasting Serum/plasma collection for correlative studies and optional banking	0,2,4,6 months
	· Glasgow Prognostic score: Full blood count (FBC), Albumin, C-reactive protein (CRP)	

### Statistical analysis

#### Sample size

A sample size of 72 evaluable participants (36/arm) provides 80% power (two-tailed α 0.05) to detect a difference of 6 points (FACT-F subscale range: 0–52) in the primary outcome measure of fatigue between the two treatment arms at 2 months and assuming a standard deviation of 9 [57]. This is a standardized effect size of 0.67, thus each of the secondary outcomes is also powered at this level. Due to the poor prognosis for this patient population we need to increase our enrolment by 30% to account for attrition. Therefore, in total we will aim to recruit ~102 patients.

#### Statistical analyses

We report only on analyses for the primary and three secondary outcomes: fatigue, quality of life, activities of daily living, and the six minute walk test. Because of the potential for informative dropout, rigorous methods which account for missing data will be employed. There are three type of missing data. Data are missing completely at random (MCAR) if missing values and observed value are not systematically different. Data are missing at random (MAR) if any systematic differences can be explained by observed outcome or covariate data. Data are missing not at random (MNAR) when systematic differences exist, even after adjusting for previously observed data. A MAR primary analysis followed by sensitivity analyses are recommended by experts in the field of missing data [58].

Thus, our main analyses will use linear mixed models for all outcomes, which are unbiased for data which are MCAR or MAR and are consistent with the intention-to-treat principle [58-60]. Mixed model account for covariance between repeated measures on patients and allow for: 1) comparing patterns of change over time by testing the intervention group by time interaction; and 2) estimating and testing differences between groups at time points of interest via linear contrasts. Unadjusted and adjusted main analyses will be carried out, with adjustment for baseline measures including sex, age, disease stage, and the baseline outcome.

Patterns of missing data will be assessed to consider potential missing data mechanisms and baseline characteristics of patients lost to follow-up at 2, 4 and 6 months will be compared to patients who completed follow-up to assess patterns of loss to follow-up. Sensitivity analyses will be carried out using multiple imputation, which will include auxiliary data such as ECOG performance status and baseline secondary outcomes such as physical activity measures.

Overall survival is an exploratory endpoint, because the study has limited power to evaluate this. Patients alive at final analysis or who have become lost to follow up will be censored at their last contact date. Overall survival will be described by the Kaplan-Meier method. A stratified log-rank test adjusting for the stratification factors of disease stage (locally advanced vs metastatic) and ECOG performance status (0+1 vs 2) at randomisation will be used to compare overall survival between the two arms.

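### Two mixed-model analyses, one unadjusted and one adjusted, are both labelled main for the single primary fatigue comparison, and the article does not say which decides

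*Protocol article*

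**What the plan says.** Three places in the protocol article bear on this point.

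- *Primary and secondary endpoints* fixes one instrument (the FACT-F subscale), one contrast and one time: "The primary outcome will be a comparison of fatigue in the intervention and control arms at the conclusion of the intervention", meaning the 2-month assessment.
- *Sample size* plans for 36 evaluable participants per arm, a 6-point difference and one test. It states that this number "provides 80% power (two-tailed α 0.05"), "assuming a standard deviation of 9".
- *Statistical analyses* chooses linear mixed models and then says "Unadjusted and adjusted main analyses will be carried out". The adjusted version uses sex, age, disease stage and the baseline value of the outcome among its baseline covariates.

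The same section calls only multiple imputation a sensitivity analysis. It also recommends a primary analysis valid under missing at random, but both mixed models fit that description, so the recommendation does not choose between them. *Methods/design* lists three stratification factors: disease stage, ECOG status and cancer centre. Of these, the adjusted analysis names only disease stage.

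**The concern.** One primary question at one significance level needs one deciding test. Here two models have the same rank, and nothing says which gives the answer if one is significant and the other is not. The choice could then be made after both results are known, and the 5% level would no longer be protected.

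The two analyses are also not interchangeable. The adjusted one uses the baseline FACT-F score, which is collected from everyone before randomisation, and will usually be more precise. Disagreement is therefore a realistic outcome, even if the intervention works as well as the design assumes.

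A statistical analysis plan that is not shown may settle the matter. The point still stands on the article as written, because it does more than leave the choice open: it gives both analyses the main label.

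**Working it through.** **Inputs from the article.** Difference 6, SD 9, two-sided α 0.05, power 80%, 36 per arm (*Sample size*); FACT-F at 2 months (*Primary and secondary endpoints*).

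**Input assumed.** ρ, the correlation between baseline and 2-month FACT-F, is not given. I use 0.4 to 0.7.

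**Approximation.** The unadjusted analysis is treated as a two-sample comparison at 2 months, and the adjusted one as an ANCOVA on baseline FACT-F, both with complete data. The planned mixed models with dropout will differ somewhat.

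**Step 1: reproduce the planned size.** n per arm = 2 × (9/6)² × (1.960 + 0.842)² = 35.3, rounded up to 36. This matches. Power at 36 per arm is 80.7% (normal) or 79.7% (t). The calculation uses one unadjusted comparison.

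**Step 2: correlation of the two test statistics.** Under no effect this is √(1 − ρ²): 0.917, 0.866, 0.800 and 0.714 for ρ = 0.4, 0.5, 0.6 and 0.7.

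**Step 3: type I error under three possible rules.** The either-test error is P(|z₁| > 1.96 or |z₂| > 1.96) from the bivariate normal. The both-tests error is 0.05 + 0.05 minus that value.

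| ρ | One named test | Either may count | Both required |
|---|---|---|---|
| 0.4 | 5% | 6.9% | 3.1% |
| 0.5 | 5% | 7.3% | 2.7% |
| 0.6 | 5% | 7.8% | 2.2% |
| 0.7 | 5% | 8.3% | 1.7% |

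A simulation at 36 per arm (40,000 replicates per value; t-test against ANCOVA on baseline, sex, age and stage) gave 7.6%, 7.8% and 8.4% for the either-test rule at ρ = 0.5, 0.6 and 0.7. Each test alone gave 4.9% to 5.1%. Two independent tests would give 1 − 0.95² = 9.75%, which is not reached because the two tests are strongly correlated.

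**Step 4: disagreement and power at the design effect.** The unadjusted statistic has mean (6/9) × √(36/2) = 2.83. The adjusted one has mean 2.83/√(1 − ρ²). The chance that exactly one is significant comes from the bivariate normal with the Step 2 correlation. Power of the adjusted test uses the t distribution with standardised effect 0.667/√(1 − ρ²).

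| ρ | Mean of adjusted z | Exactly one significant | Power, adjusted |
|---|---|---|---|
| 0.4 | 3.09 | 9% | 86% |
| 0.5 | 3.27 | 12% | 90% |
| 0.6 | 3.54 | 15% | 94% |
| 0.7 | 3.96 | 18% | 97% |

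Most of the disagreement is the adjusted test being significant when the unadjusted one is not. At ρ = 0.5 that accounts for 10.9 of the 12.2 percentage points.

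**The case against.** The strongest reply is that the article contains no rule letting the trial claim success on either test. A reader might infer from two main analyses that the type I error is above 5%. The text does not support this: each test alone holds 5%, and requiring both would give less than 5%. The 6.9% to 8.3% belongs to one rule that the wording leaves possible. This objection stands, so the excess must be stated conditionally.

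It is also fair that ρ is not in the article, that the calculation replaces longitudinal models by a simpler pair of tests, and that the excess is at most about 3.3 percentage points over the assumed range.

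Three further inferences are tempting and should not be drawn.

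- **Baseline FACT-F enters the model twice, as response and as covariate.** The article gives assessments at 0, 2, 4 and 6 months, but that is a visit schedule. It does not say that month 0 is a response in the adjusted model. Responses at 2, 4 and 6 months with baseline as covariate fit the text fully.
- **The open covariate list is a defect in itself.** The main covariates are named, and closing the list is detail that an article normally leaves to the analysis plan.
- **Running the unadjusted analysis wastes precision.** The adjusted analysis is already planned. The power figures are a reason to prefer it as primary; they do not show an error in the sample size, which reproduces.

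The endpoint, instrument and time point are all settled, and linear contrasts at chosen time points are provided for. What remains open is narrow: which of the two models decides. None of the objections resolves that.

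**Conclusion.** The point holds in a limited form. The article gives two analyses equal standing for one primary comparison and has no rule for discordant results. That follows from the text and needs no assumption.

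Its numerical consequence is conditional. The either-test error of about 6.9% to 8.3% requires that success may be claimed on whichever test is significant. Both that range and the 9% to 18% chance of disagreement at the design effect also rest on ρ between 0.4 and 0.7 and on the complete-data approximation. The documents do not show that the 5% level is exceeded.

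This is a should-fix. Sample size, endpoint and data collection are unaffected, but the choice cannot be made credibly once both results are known.

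**What to change.** Before any outcome data are compared by arm, name one primary test: the 2-month arm contrast in FACT-F from the linear mixed model, adjusted for baseline FACT-F, the stratification factors (disease stage, ECOG status, centre), age and sex, at two-sided 5%. Label the unadjusted analysis supportive, and state that it does not decide the primary question.

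The adjusted contrast is the better choice because it uses a baseline score already collected and brings in the two stratification factors that the adjusted analysis does not now name.

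The cost is a sentence or two of wording. No extra patients, visits or measurements are needed. Type I error is then that of one named test, 5%, and under the assumptions above power at 36 per arm goes from about 80% to about 86% to 97%.

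### ECOG status and centre stratify the randomisation but are not named as covariates in the adjusted main model: a small, conservative mismatch that is cheap to remove

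*Protocol article*

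**What the plan says.** Methods/design sets three stratification factors: disease stage (locally advanced or metastatic), and "ECOG performance status (0–1 versus 2), and cancer centre". Recruitment is from four hospitals.

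Statistical analyses specifies linear mixed models for fatigue and the secondary outcomes, run both unadjusted and adjusted, and calls both main analyses. The adjusted version is fitted "with adjustment for baseline measures including sex, age, disease stage, and the baseline outcome". Of the stratification factors, only stage is on that list.

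ECOG status has two other roles in the same section. It is an auxiliary variable for the multiple-imputation sensitivity analysis, and it enters the survival comparison: "A stratified log-rank test adjusting for the stratification factors of disease stage (locally advanced vs metastatic) and ECOG performance status (0+1 vs 2". Survival is labelled exploratory. Centre is not mentioned in any analysis.

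The main analysis is justified under MAR, which the article explains in terms of what observed outcomes and covariates can account for. It also warns that dropout may be informative.

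**The concern.** Stratified allocation makes the arms more alike on the stratifying factors than simple randomisation would. A model that leaves out a prognostic stratifier does not credit that balance: the variation the factor explains stays in the residual, so the standard error of the treatment difference is too large. The interval is then over-wide and the test runs below its nominal level.

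The plan is also uneven. It carries ECOG status into the test for an exploratory endpoint but does not name it for the primary one.

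There is a missing-data side as well. Using ECOG status as an imputation auxiliary treats it as informative about missing values. A mixed model without it is valid under MAR only given what is in the model, so dropout that depends on ECOG status beyond stage, baseline fatigue and the observed repeated scores falls outside that assumption.

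**Working it through.** **1. The plan's own figure.** Inputs from Sample size: "A sample size of 72 evaluable participants (36/arm" in each group, a 6-point difference, "assuming a standard deviation of 9", two-sided 0.05.

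- SE = 9 × √(2/36) = 2.121, and 6/2.121 = 2.828.
- Power = Φ(2.828 − 1.960) = Φ(0.868) = 0.807 (0.797 by the noncentral t).

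The stated 80% reproduces. It does not depend on covariates.

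**2. Bound for an otherwise unadjusted comparison.** The article gives no prognostic strength for ECOG status or centre. Let R² be the share of residual variance they explain (an assumption), with strata exactly balanced between arms. The true SE is then √(1 − R²) times the reported one.

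- SE overstatement = 1/√(1 − R²) − 1
- Type I error = 2[1 − Φ(1.960/√(1 − R²))]
- Power, factors omitted = Φ(0.868/√(1 − R²))
- Power, factors included = Φ(2.828/√(1 − R²) − 1.960)

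| R² | SE too wide by | Type I error | Power omitted | Power included |
|---|---|---|---|---|
| 0 | 0% | 0.050 | 0.807 | 0.807 |
| 0.05 | 2.6% | 0.044 | 0.814 | 0.827 |
| 0.10 | 5.4% | 0.039 | 0.820 | 0.846 |
| 0.20 | 11.8% | 0.028 | 0.834 | 0.885 |

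In every row the power with the factors omitted stays above 80%.

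**3. The model the plan describes.** The adjusted model already contains stage and baseline fatigue, which take up part of what ECOG status explains. This was simulated: 3,000 trials per scenario, N = 72, blocks of four within 2 × 2 × 4 = 16 strata, analysed at the 2-month visit without missing data. Assumptions: baseline correlation 0.5, 70% metastatic, 20% ECOG 2, fatigue score 6 or 9 points worse with ECOG 2, centre SD 1.5 to 3. Age and sex were not simulated. Three models were fitted to each data set: unadjusted; stage plus baseline fatigue; and these plus ECOG status and centre.

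| ECOG effect, centre SD | Type I: unadjusted | Type I: stage + baseline | Power: stage + baseline | Power: plus ECOG and centre |
|---|---|---|---|---|
| 0, 0 | 0.057 | 0.056 | 0.885 | 0.879 |
| 6, 1.5 | 0.042 | 0.050 | 0.913 | 0.921 |
| 9, 2 | 0.035 | 0.047 | 0.947 | 0.951 |
| 9, 3 | 0.026 | 0.043 | 0.942 | 0.959 |

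The Monte Carlo error of a 5% rejection rate is √(0.05 × 0.95/3000) = 0.004, so the first row is compatible with 0.05.

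In the three prognostic scenarios, the ratio of mean model SE to empirical SE for stage plus baseline runs from 1.781/1.796 = 0.992 to 1.671/1.610 = 1.038, that is, about −1% to +4%. Adding ECOG status and centre gains 0.4 to 1.6 power points. With no prognostic effect it gains nothing.

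**4. Missing data.** No arithmetic is possible, because the article gives neither dropout by ECOG status nor the relation of ECOG status to fatigue. Bias in the treatment difference would need more than dropout related to ECOG status: in an additive model that loss must differ between arms, or the treatment effect must vary with ECOG status.

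**The case against.** The strongest reply is that the covariate list opens with *including* and that a journal article condenses the full plan, so the complete model may hold all three factors. For centre this largely stands: the article is silent, and silence is not exclusion. For ECOG status it is weaker, because the article gives it the role of an imputation auxiliary, which normally means a variable outside the analysis model, and names it explicitly for survival.

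A reader might infer from the bound in step 2 that the adjusted analysis runs at a type I error near 2.8% and forfeits about 5 power points. The document does not support that. Those values need 20% of residual variance explained and exact balance within strata, and they describe a comparison without baseline adjustment. With 72 evaluable patients over 16 strata (4.5 each on average), exact balance is unlikely.

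A reader might also infer that wrong standard errors threaten a false positive. The error goes the other way.

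On missing data, the planned safeguards are real: likelihood-based use of all observed scores, a comparison of patients lost and retained, and imputation that brings in ECOG status. They reduce the concern without placing ECOG status in the main model.

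Whether centre is fitted as fixed or random is a matter of judgement.

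**Conclusion.** The mismatch is real but modest. Two of the three stratification factors are not named in the adjusted main model, and ECOG status is in effect assigned elsewhere.

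The consequence is conservative only. For the adjusted model it is about 0–4% in the standard error and 0–2 power points; for the unadjusted main analysis, simulated type I error is about 0.026–0.042; it is nil if the factors do not predict fatigue. The planned 80% power is not endangered.

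These sizes rest on assumed effects of ECOG status and centre, an assumed blocking scheme and a single-visit analysis of complete data. The MAR point holds in direction, but its size is unknown. The case for changing the plan is consistency with the randomisation and a better-supported MAR assumption at almost no cost, rather than rescue of an invalid analysis.

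**What to change.** In Statistical analyses, state that the adjusted mixed model for fatigue and each secondary outcome includes disease stage, ECOG status (0–1 versus 2) and centre, together with the baseline outcome, age and sex. State in advance how a very small centre will be handled, for example by pooling. Fixed or random centre effects are both acceptable if the choice is written down beforehand.

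The cost is one sentence and, with centre fixed, 1 + 3 = 4 degrees of freedom out of about 70 (72 − 2). No extra data are needed, since both factors are recorded at randomisation. The sample size is unchanged. The unadjusted analysis is not altered by this and would remain conservative if the factors are prognostic.
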